## Abstract

**Background:**

Children’s online media perpetuates appearance idealised images and can negatively impact the way children feel about their own and other people’s bodies (e.g., weight bias) at a young age. The development and evaluation of body image interventions for young children to counteract this, are scarce. There is a need for prevention efforts to nurture the development of positive body image among this group to help mitigate potential body image concerns in later childhood. Media-based approaches promoting positive body image messages have shown preliminary efficacy. In collaboration with industry partners, we have developed two positive body image media micro-interventions (a 15-minute episode and a music video) to be evaluated in a fully powered RCT.

**Methods:**

We aim to recruit 440 children between the ages of 4 and 6 years to be randomised into one of four conditions: (i) 15-minute episode intervention, (ii) 15-minute episode control, (iii) 3-minute music video intervention, or (iv) 3-minute music video control. This study will be conducted face-to-face, whereby children and a parent attend a media screening session and children complete pre-and post-intervention measures of positive body image and weight bias. Both the child and parent will watch their assigned media, together on a tablet device. Due to their age, children will complete outcome measures with a trained moderator in a play-based interview pre-intervention (T1), immediately post-intervention (T2) and one-week follow up (T3). A corresponding parent will complete a questionnaire on intervention acceptability at T2, and re-watch of their assigned media at T3. The primary outcome will be the change in body appreciation, and secondary outcomes include change in functionality appreciation and weight bias. Exploratory analyses will determine any effect of gender (girls vs. boys), year group (reception vs. year 1) dosage or delayed effects. Moderator fidelity will be also assessed.

**Discussion:**

This study will evaluate two positive body image micro-interventions among children 4–6 years old. These interventions have the potential to bolster children’s positive body image and reduce weight bias. A dissemination plan is in place with project stakeholders such that the interventions can reach millions of children worldwide.

**Trial registration:**

The trial is registered with Clinical Trial.gov, Ref number: NCT06146647.

**Supplementary Information:**

The online version contains supplementary material available at 10.1186/s12889-024-20869-z.

## Background

### Body image in childhood

Body image – the way people think, feel, and behave in relation to their body – encompasses two distinct constructs; negative body image (i.e., body dissatisfaction) and positive body image (i.e., an overarching love, respect, appreciation for, and acceptance of the body and what it can do [1]). Traditionally, body dissatisfaction has been viewed as a problem that develops during adolescence; however, such concerns may develop much earlier than this [2, 3]. Typically, very young children (e.g., ages 3–5 years) express positive feelings towards their bodies [4], with some beginning to report body dissatisfaction during early years of schooling [5]. Negative attitudes towards other people’s bodies, particularly weight bias, can emerge as early as three years ( [6]). By age five years, many children have internalised appearance ideals [7] and by age six, a large proportion of children (up to 70%) report dissatisfaction with specific body parts, weight and/or shape [8, 9], and a desire to be thinner or more muscular for girls and boys respectively [5, 10]. Body dissatisfaction becomes problematic when high value or investment is placed upon appearance [11]. Appearance investment often peaks as children emerge into pre-adolescence, a period when body dissatisfaction can become entrenched [12]. Together, this highlights a small but unique window of opportunity to shape and nurture the development of positive body image among younger children to harness their existing positive attitudes and potentially prevent the future onset of body dissatisfaction.

### The role and impact of the media

Sociocultural theory (Tripartite Model of Influence^1^; [13]) suggests children’s media, particularly those promoting appearance-idealised messaging, significantly influences the onset and development of body dissatisfaction. Children’s media plays a pivotal role in learning [14] including teaching children about beauty and the value of appearance. Content analyses of children’s TV, music, and film over the past few decades underscores the prevalence of characters who conform to cultural appearance ideals with female characters being thin or slender (e.g., *Disney princesses like Elsa from Frozen)* and male characters being muscular, strong, and athletic, such as characters like *the Incredibles or* superheroes *like Spiderman* [15–17]. Positive qualities such as being attractive (and having love interests), popular, happy, and intelligent are often attributed to thinner characters [18, 19]. In contrast, larger characters are less frequently seen on screen and more likely to be portrayed negatively [20]; have limited social connections, be subject to teasing, considered lazy, depicted as less intellectually capable, or characterised as a villain [21–23]. A few examples include, *Augustus Gloop* from *Charlie and the Chocolate Factory*, *Ursula the Sea Witch*,* and The Hunchback of Notre Dame*. This is also evidenced by data with a recent study highlighting 84% of children’s top grossing films from 2012 to 2015 included verbal insults about body size or weight [24]. As the Tripartite Model [13] suggests, these messages become internalised, and repeat exposure to this type of media reinforces gendered appearance stereotypes [25].

In recent years, where young children go to consume media content has proliferated. In addition to TV viewing, children now have unlimited access to media through online platforms such as Netflix and YouTube (i.e., YouTube Kids). A recent survey found 80% of children aged 0–7 years were subscribed to YouTube, spending an average 1.4 h per day consuming media content [26]. YouTube not only offers long form content in the style of TV episodes but also a plethora of short form content (e.g., music videos) which has become the most popular form of children’s content on YouTube [27]. Notably, ‘*Baby Shark’*, a 2-minute 17-second music video for children, became the first YouTube video to reach over 10 billion views [28] and the most watched video on the platform.

Since the COVID-19 pandemic, streaming platforms such as YouTube, have also become an online learning tool for children, offering interactive videos from popular children’s shows on varied topics including mathematics, languages, understanding emotions, and friendships [29]. However, a large proportion of this content, including animation and cartoons, features appearance-idealistic themes such as positive messaging about being thin and attractive [20, 30]. Others use humour to promote prejudiced attitudes, much like media elsewhere. For example, ‘*Peppa Pig’*, an animated show which follows Peppa’s adventures with her family and friends and teaches children about daily activities, includes characters who engage in negative body talk, exhibiting weight biased attitudes. For example, Peppa tells Daddy pig he needs to get fit as he is ‘a bit too fat’, making jokes about his ‘big tummy’; when Daddy Pig tries to join Peppa in her treehouse he gets wedged in the door whilst the other characters laugh (episode 37 or 42, season 1).

Frequent exposure to media promoting appearance-idealised images and weight stigmatising messages comes with consequences for children and adolescents, especially children who are higher weight. Higher weight children are stigmatised in school and recreational settings (e.g., have less friends, be the victims of teasing and bullying [31]), which can lead to increased social isolation, more internalised weight bias, and the exacerbation of body dissatisfaction [32, 33]. More generally, body dissatisfaction can lead to other psychological and social concerns as children transition from childhood into adolescence including elevated stress, anxiety, low mood, disordered eating (e.g., dietary restraint; [34]), decreased academic achievement and increased disengagement from various aspects of life (e.g., dropping out of sport and avoiding social interactions; [35]).

### Strategies and interventions for children

Despite Smolak and Levine’s ( [36]) call for prevention efforts to promote positive body image among young children more than two decades ago, progress has been limited. Targeting body dissatisfaction is challenging once concerns are entrenched; intervention strategies tend to be lengthy, costly, and intensive, only a handful have proven efficacy and there are additional barriers (e.g., funding, access) to implementation [37]. Instead, experts recommend shifting the focus to prevention at a group level among younger demographics, so that a whole population is less exposed to and more resilient to risk factors [38]. One way to achieve this is to bolster children’s positive body image by broadening their conceptualisation, and acceptance of diverse appearances [35] and foster resilience to appearance-ideal messages ( [3, 39]). Consequently, this serves as a protective factor against the adverse effects of appearance-idealised media exposure.

Leveraging media is a key strategy for young children, as storytelling and role modelling are primary avenues for learning [40]. Numerous TV shows have successfully adopted this approach to enhance children’s empathy, self-efficacy, emotional competence, school readiness and pro-social behaviour; *Sesame St* [41], *Daniels Tiger in the Neighbourhood* [42], and *Blues Clues* [43]. Moreover, there has been a recent surge in media content, particularly within the Disney franchise, aiming to increase representation more broadly. This is exemplified by the release of films like *Moana*, *Encanto*, and *Coco* which feature characters, particularly protagonists, from diverse ethnic backgrounds and a range of body sizes [44]. However, such content has not been empirically evaluated.

To date, three media-based interventions designed to foster positive body image among young children (i.e., 9 years and under) have been empirically evaluated. The first study evaluated ‘*Shapesville’*, a picture based book promoting self-acceptance and appearance diversity, among girls aged 5–9 years [45]. *Shapesville* was found to generate immediate improvements in appearance satisfaction which were maintained at 6-weeks follow up, relative to a waitlist control. Most interestingly, girls’ recognition of their own special talents, a positive body image theme woven into the book's storyline, significantly increased at post-intervention relative to the control group. The impact of the book on young boys’ body image and related attitudes is unknown. The second study evaluated a series of 60-second animated ‘micro-interventions’ centred around the children’s TV series *‘Steven Universe and the Crystal Gems’* [46]. The videos targeted risk and protective factors for body image among boys and girls aged 7–10 years and resulted in immediate improvements in state body satisfaction and sustained effects in trait media literacy and appearance teasing. Unexpectedly, the control performed in line with the intervention condition. This finding was attributed to the inclusion of characters of diverse body shapes and sizes in the control episode, indicating that representation of diverse body sizes on its own could be a successful strategy to improve children’s body image. The third study evaluated a theatrical production of ‘*Cinderella – The AWESOME Truth!’* [47], designed to increase children’s (aged 5–9 years) body appreciation. Despite the lack of a control group in the study’s research design, the performance was associated with improved state body appreciation, self-perceived uniqueness and self-perceived ‘awesomeness’.

#### Micro-interventions

Together these studies highlight the potential of embedding positive body image messaging within different forms of children’s media to foster positive body image and in-particular the innovative use of micro-interventions. Micro-interventions are low-intensity, brief interventions, designed to deliver in the moment (e.g., state-based) benefits to an individual’s mental health [46, 48]. Micro-interventions are particularly well suited for children due to their limited attention span and developmental capacity ( [46]) and have proven efficacy in delivering immediate benefits to pre-adolescent’s and adolescent’s body image (e.g [49, 50]). They can also be easily integrated into media environments that children are avid consumers of, such as YouTube, however the use of micro-interventions among young children is yet to be explored.

### Aims

The aims of this paper are to (1) outline the development of two positive body image media micro-interventions (a 15-minute episode and 3-minute music video) designed for children aged 4–6-year-olds, (2) describe how these interventions will be evaluated, (3) detail the plans for dissemination, and (4) discuss the study’s potential strengths and limitations.

The described study is a randomised controlled trial which aims to assess the effectiveness and acceptability of the two interventions among young children. Our primary research questions and hypotheses are:

RQ1. Relative to time-matched active controls, are the two positive body image media micro-interventions effective in yielding immediate improvements in children’s body appreciation (primary outcome) and functionality appreciation and in reducing weight bias (secondary outcomes)?H1: We anticipate children randomised into one of the intervention conditions to experience an immediate improvement (T2) in body appreciation and functionality appreciation, relative to the control groups. We also expect the intervention groups to report an immediate reduction in weight bias (T2), relative to the control groups.RQ2. Are the two positive body image media micro-interventions acceptable to children and their participating parent/guardian?H2. We expect the two positive body image media micro-interventions to be enjoyed by children and viewed as age appropriate and relevant by their participating parent/guardian.

In addition, to our knowledge, these are the first media-based interventions targeting positive body image, designed for very young children. As such, we plan to also test five secondary exploratory research questions, examining two hypothesised moderators, the effects of exposure to positive body image media content via repeat watching and due to the duration of the media, as well as sustained effects.

#### Moderators

RQ3. Does gender moderate intervention effectiveness?H3. We predict that the interventions will be more effective for girls than for boys.RQ4. Does year group moderate intervention effectiveness?H4. We predict that the interventions will be more effective for children in Year 1 (ages 5 and 6) than children in Reception (ages 4 and 5).

#### Exposure effects

RQ5. Are there within-group intervention effects whereby repeated exposure to either one of the positive body image media micro-interventions is positively correlated with improvements at T3?H5. We expect that children within each intervention condition (e.g., 15-minute episode and music video) will experience greater improvements to functionality appreciation and body appreciation and greater reductions in weight bias, at one-week follow up (T3) the more they have watched their content from T2 to T3.RQ6. Is there a difference in terms of the immediate pre-post effectiveness outcomes between the two interventions?H6. We anticipate the 15-minute intervention will be more effective than the music video on the premise that there will be greater exposure to core messaging.

#### Sustained effects

RQ7. Do we observe sustained effects approximately one week following media exposure, controlling for repeat watching?H7. We anticipate children to report sustained effects at one-week follow up (T3), relative to the control groups based on parent-child conversations on topics related to positive body image.

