#### Repeat watching

In between post-intervention (T2) and follow-up (T3), parents will be given access to their assigned media content via a secure link and encouraged to rewatch it with their child before they return for their next session in approximately seven-ten days’ time. Parent’s will self-report how many times they re-watched their content in their T3 follow-up survey.

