The above analysis plan for body appreciation will be repeated for the secondary outcome measures of functionality appreciation and weight bias. Secondary research questions at T3 will be examined using the same analysis of covariance methods controlling for baseline (T1).

The aim is to have ITT data on *N* = 420 participants. This will be achieved through a target recruitment of *N* = 440 cognisant that some potential participants might be unable to partake in the research due to external mitigating reasons. If the size of the ITT analysis set is N > = 380 then the data will be analysed as given. If the size of the ITT analysis set due to missing data is between 260 and 380 then a full missing values analysis will be undertaken, and appropriate sensitivity analyses performed. If the size of the ITT analysis set due to missing data is less than 260 then results will be given descriptively.

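### RQ7 adjusts the randomised T3 comparison for repeat watching, which happens after randomisation; the analysis section names only T1, so the two describe different estimands and need reconciling

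*Protocol article*

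**What the plan says.** Under Sustained effects, RQ7 asks: "Do we observe sustained effects approximately one week following media exposure, controlling for repeat watching". H7 makes it a comparison of randomised groups, "We anticipate children to report sustained effects at one-week follow up (T3), relative to the control groups", and gives the expected mechanism: "based on parent-child conversations on topics related to positive body image".

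Under Repeat watching, between T2 and T3 "parents will be given access to their assigned media content via a secure link and encouraged to rewatch it with their child". Every arm receives this for its own media. The count is parent-reported: parents "will self-report how many times they re-watched their content in their T3 follow-up survey".

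Under Exposure effects, RQ5 asks whether, within group, "repeated exposure to either one of the positive body image media micro-interventions is positively correlated with improvements at T3". H5 expects greater improvement "at one-week follow up (T3) the more they have watched their content from T2 to T3".

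Under Statistical analyses: "Secondary research questions at T3 will be examined using the same analysis of covariance methods controlling for baseline (T1". Repeat watching is not mentioned there. The same section says conclusions rest on the intention-to-treat set. The Aims section classes RQ3 to RQ7 as secondary and exploratory.

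**The concern.** Re-watching is a behaviour that follows both randomisation and the first viewing. It concerns each arm's own video, so the assigned content could change how often it is watched again. By the protocol's own H5, it also affects the T3 outcome in the intervention arms. RQ7 as worded therefore conditions a randomised contrast on a possible mediator.

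Two things can follow. First, any part of the effect that travels through re-watching is removed, so the estimate is no longer the total effect of being assigned the video. Second, if something unmeasured, such as family engagement, raises both re-watching and the child's T3 score, conditioning on re-watching opens a path between arm and outcome, and the result is not a clean direct effect either.

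An analyst who follows RQ7 and one who follows the Statistical analyses section would fit different models and could report different answers to the trial's only question about persistence.

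**Working it through.** **Plan's own figure.** The only stated calculation is for T2. With two-sided alpha 0.05, 90% power, d = 0.3 and r = 0.75, n per arm = 2(1.960 + 1.282)² × (1 − 0.75²) / 0.3² = 102.16, so 103; the protocol states 103. The second scenario (d = 0.25, r = 0.8, 80% power) gives 90.4, so 91, or 92 with the t distribution; the protocol states 92. Both reproduce. Neither bears on RQ7, for which no figure is stated.

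**The two models.** The analysis section implies T3 score on arm + T1. RQ7 implies T3 score on arm + T1 + re-watch count.

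**Inputs assumed here (none is in the documents).** Let A be the arm, M re-watching (within-arm SD 1) and U an unmeasured shared cause:

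- M = aA + uU + noise
- T3 = δA + 0.75·T1 + bM + gU + noise, with g = 0.66u

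Here a is the arm difference in re-watching, b the effect of re-watching on T3, and δ = 0.30 the effect not passing through re-watching. The factor 0.66 is √(1 − 0.75²), so U correlates at about u with both re-watching and the T1-adjusted outcome. Using r = 0.75 at T3 is itself an assumption, since the protocol gives it for immediate pre-post scores. Effects are in units of the T3 outcome SD when b = 0.

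**Formulae.**

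- T1-only model estimates the total effect: δ + ab
- Re-watch-adjusted model estimates: δ − 0.66·a·u²
- Adjusted minus T1-only: −a(b + 0.66u²)
- Adjusted minus direct effect δ: −0.66·a·u²

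With u = 0.5, 0.66u² = 0.165. For example, a = 0.5 and b = 0.2 give −0.5 × (0.2 + 0.165) = −0.18.

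**Simulation (1,000,000 children per setting; differences taken before rounding).**

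| a | b | u | T1-only | Adjusted | Difference |
|---|---|---|---|---|---|
| 0 | 0.2 | 0.5 | 0.302 | 0.302 | 0.000 |
| 0.5 | 0 | 0 | 0.301 | 0.301 | 0.000 |
| 0.2 | 0.2 | 0 | 0.339 | 0.298 | −0.040 |
| 0.2 | 0 | 0.5 | 0.297 | 0.264 | −0.033 |
| 0.2 | 0.2 | 0.5 | 0.338 | 0.266 | −0.072 |
| 0.5 | 0.2 | 0 | 0.401 | 0.301 | −0.100 |
| 0.5 | 0 | 0.5 | 0.300 | 0.218 | −0.083 |
| 0.5 | 0.2 | 0.5 | 0.402 | 0.220 | −0.183 |
| −0.3 | 0.2 | 0.5 | 0.242 | 0.351 | +0.109 |

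Reading the table:

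- With a = 0 the models agree. They also agree when re-watching is unrelated to outcome (b = 0, u = 0).
- With u = 0 and b = 0.2 the adjusted model returns the direct effect of 0.30. The gap from the total effect is then a change of estimand, not bias for the direct effect.
- With u = 0.5 the adjusted model misses the direct effect as well, by about −0.03 (a = 0.2), −0.08 (a = 0.5) or +0.05 (a = −0.3).

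**False-positive rate.** With no true arm effect, b = 0, u = 0.5 and 105 per arm (8,000 trials each), the adjusted test rejected in about 0.05 (a = 0), 0.07 (a = 0.2) and 0.14 (a = 0.5) of trials. The T1-only test stayed at about 0.05 throughout.

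**The case against.** The strongest reply is that RQ7 means what it says. H7 credits conversations at home, and H5 deals with re-watching separately, so RQ7 can be read as asking for an effect that is not due to re-watching. Removing that pathway would then be the aim. This stands as a reading of intent. What it does not supply is the estimand itself or the assumption it needs, namely no unmeasured common cause of re-watching and outcome, and the document states neither. Co-viewing is also an obvious occasion for the conversations H7 has in mind, so adjustment could remove part of the named mechanism.

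Second, every arm gets the same encouragement, and the controls are Blippi media chosen for similar length and format, so re-watching may be balanced. That is possible, and the difference would then be about zero. The documents neither show nor exclude it.

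Third, a reader might infer that the protocol contradicts itself. It does not quite: the analysis section is silent on re-watching and does not rule it out. This is a mismatch, and the T1-only model that section implies is already close to the recommended one.

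Fourth, a reader might infer that RQ5 is invalid and needs a new between-arm model. RQ5 asks only for a within-group correlation, and how that is fitted can be left to the analysis plan. The point that remains is interpretive. The abstract speaks of dosage and the Discussion of dose response, yet engaged families, or those whose child already responded at T2, may re-watch more. A within-arm slope cannot separate that from a dose effect.

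**Conclusion.** The point holds as a mismatch between the research question and the analysis section, with a conditional risk to the T3 estimate. RQ7 conditions a randomised contrast on a parent-reported behaviour after randomisation that the protocol itself expects to influence the outcome. The analysis section names T1 alone.

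It cannot be said that the T3 effect will be biased. A difference between the models needs the arms to differ in re-watching, and re-watching to be related to the T3 outcome. Bias for the direct effect further needs a shared unmeasured cause. The range of about −0.18 to +0.11 SD, and the false-positive rates of up to 0.14, come entirely from assumed inputs. They show the order of what is possible and do not predict this trial. They should not be expressed as a share of d = 0.3, which is the T2 design effect; no T3 effect is stated.

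The consequence is confined to exploratory T3 questions. The T2 primary analysis, its power and the sample size are untouched.

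**What to change.** Reconcile RQ7 with the Statistical analyses section before the T3 data are analysed:

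1. Make the intention-to-treat arm contrast at T3, adjusted for T1, the main RQ7 analysis. Describe it as the effect of the supervised viewing plus encouraged home re-watching.
2. Report the distribution of re-watch counts by arm, so readers can see whether the arms differ.
3. Remove the repeat-watching condition from the main RQ7 question. If the direct effect is of interest, keep the re-watch-adjusted model as a labelled exploratory mediation analysis. State its assumptions, in particular no unmeasured common cause of re-watching and T3 outcome, and note that the count is parent-reported.
4. Report RQ5 as a within-arm association and avoid causal dose language for it.

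The cost is a wording change and the relabelling of one model. No new data are needed, since the re-watch count is already collected, and no sample size or power figure changes.

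### RQ7 asks for the T3 arm contrast adjusted for repeat watching, a post-randomisation variable; the one stated T3 model adjusts for T1 only, and that model should answer RQ7

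*Protocol article*

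**What the plan says.** Three parts of the protocol article bear on the T3 comparison.

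- **The question (Aims, Sustained effects).** RQ7 asks: "Do we observe sustained effects approximately one week following media exposure, controlling for repeat watching". H7 makes it a between-arm contrast: "We anticipate children to report sustained effects at one-week follow up (T3), relative to the control groups". It gives parent-child conversations as the reason for expecting an effect. The Aims class this among five secondary exploratory questions.
- **The model (Statistical analyses).** "Secondary research questions at T3 will be examined using the same analysis of covariance methods controlling for baseline (T1"). Repeat watching is not named there.
- **The covariate (Repeat watching; Procedure).** "In between post-intervention (T2) and follow-up (T3), parents will be given access to their assigned media content via a secure link", and they are "encouraged to rewatch it with their child before they return for their next session". At T3 they "self-report how many times they re-watched their content in their T3 follow-up survey". Each family re-watches its own film: body-image content in the intervention arms, a dental or tooth-brushing film in the controls.

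H5 (Exposure effects) expects larger improvements within each intervention arm "the more they have watched their content from T2 to T3".

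**The concern.** A covariate measured before randomisation leaves the arm contrast a randomised one. Repeat watching is not such a covariate. It follows assignment, the family chooses it, and the assigned film may change it. Family traits, such as general engagement, could raise both the number of viewings and the child's T3 answers. Families with equal counts in the two arms are then no longer comparable in those traits if one film is replayed more readily than the other.

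H5 also makes re-watching one way in which the intervention works, so the adjustment can take out part of the effect that was randomised. In addition, one viewing of a dental film is not the same exposure as one viewing of the body-image film. A single slope for both does not isolate what remains of the first screening.

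At stake is the H7 conclusion. A false sustained effect could appear or a real one be hidden, in a direction set by which film families happen to replay.

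**Working it through.** **1. The plan's own figure.** Statistical power and sample size gives 103 per arm for d = 0.3, r = 0.75, two-sided alpha 0.05 and 90% power. With n = 2(1 - r²)(z₀.₉₇₅ + z₀.₉₀)²/d² = 2 × 0.4375 × (1.960 + 1.282)²/0.09 = 102.2, this rounds up to 103 and is reproduced. It concerns T2 only, so the point below does not touch it.

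**2. What the adjustment does.** For least squares, apart from chance differences in T1:

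adjusted contrast = T1-only contrast - (slope on re-watch count) × (difference in mean re-watch count between arms).

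The T1-only contrast is protected by randomisation. The second term is zero only if the arms re-watch equally or the slope is zero. A family trait that drives both re-watching and outcome makes the slope positive even when the film does nothing.

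**3. Size when the film has no effect.** The inputs are assumptions, except 105 per arm, which is the plan's analysis target:

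- T1-T3 correlation 0.6 and total outcome variance 1;
- Poisson re-watch counts with control mean 2;
- a family trait that raises the log re-watch rate by 0.6 per SD and the T3 outcome by 0.35 SD (range 0.3 to 0.4), so residual variance is 1 - 0.36 - 0.1225 = 0.5175;
- one slope for both arms.

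| Intervention re-watching relative to control | Difference in means | Adjusted contrast (SD) | Rejection, adjusted | Rejection, T1 only |
|---|---|---|---|---|
| 0.5x | 1 - 2 = -1 | +0.12 (0.10 to 0.14) | 20% (15 to 24%) | about 5% |
| 0.67x | 1.34 - 2 = -0.66 | +0.07 to +0.09 | 10 to 13% | about 5% |
| 0.9x to 1.1x | -0.2 to +0.2 | within about 0.02 of zero | about 5 to 6% | about 5% |
| 1.5x | 3 - 2 = +1 | -0.08 to -0.11 | 11 to 18% | about 5% |
| 2x | 4 - 2 = +2 | -0.17 (-0.15 to -0.20) | 33% (24 to 42%) | about 5% |

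The identity in step 2 agrees: the implied slopes are 0.12/1 = 0.12 SD per viewing at 0.5x and 0.17/2 = 0.085 at 2x.

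**4. Masking a true effect.** A second set of assumptions uses T1-T3 correlation 0.75, 1.5 re-watches for a typical control family, log re-watch rate raised by 0.5 per SD of the trait, and a trait effect of 0.3 SD. With a true effect of 0.30 SD and the intervention film re-watched twice as often, the T1-only model gives 0.30 SD with 90% power. The adjusted model gives 0.16 SD with 41%.

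**5. Does the adjustment isolate an effect net of re-watching?** Suppose the first screening leaves nothing at T3, each viewing of the body-image film adds 0.1 SD, control viewings add nothing, and both arms average 2 viewings. The total effect is 0.1 × 2 = 0.20 SD. The difference in means is zero, so by step 2 the common-slope model returns the same 0.20 SD as the T1-only model. Simulation agrees: both give 0.20 SD and are significant in about 42% of trials. The adjusted result would be read as net of re-watching although all of it came from re-watching.

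**The case against.** The strongest reply is that the protocol already states the recommended model. Statistical analyses gives T3 ANCOVA adjusted for T1; the re-watch phrase stands only in a research question. A reader might infer that two conflicting T3 models are specified. The text does not support that: there is one model and one phrase not reconciled with it, and an unseen analysis plan may settle the matter. What remains is that the adjustment is written into the question itself, so the article points two ways on what RQ7 estimates.

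A second reply is that RQ7 may intend a direct effect, so that removing the re-watch route is the purpose. That is a legitimate question. With no common cause of re-watching and outcome, and the same effect per viewing in both arms, the adjustment does recover it: with a direct effect set at 0.15 SD and a total of 0.32 SD, the adjusted model returns 0.15. But the no-common-cause assumption is not secured by adding a covariate, and equal effects per viewing are implausible for two different films.

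Third, the arms were made alike in brand, length and format, with the same link and encouragement, and families learn their condition only at the T3 debrief. This makes similar re-watching plausible without guaranteeing it. It rules out saying flatly that the T3 comparison has an inflated error rate.

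Fourth, a reader might take the 33% rejection at 2x as false sustained effects. It is not: those rejections point against the intervention, and virtually none favour it. A false result for H7 needs the intervention film to be replayed clearly less often than the control film.

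**Conclusion.** The point holds in a limited form. RQ7 ties a between-arm contrast at T3 to a post-randomisation variable that the assigned film may change and that H5 places on the causal path, while the stated T3 model leaves it out. If RQ7 is analysed as worded, the contrast loses the protection of randomisation.

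The harm depends on unequal re-watching between arms and on an unmeasured common cause of re-watching and outcome, or on a re-watching effect that the adjustment removes. The protocol quantifies none of these, so the biases of roughly +0.12 SD at half and -0.17 SD at twice the control rate are illustrations under stated assumptions. At about equal rates there is no material bias under the null, but the common-slope adjustment then also achieves nothing towards its apparent purpose.

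RQ7 is exploratory. The primary T2 analysis and the sample size stand.

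**What to change.** 1. In Aims, Sustained effects, remove the condition on repeat watching from RQ7.
2. In Statistical analyses, state that RQ7 is answered by arm plus T1 score, for each intervention against its own control. Describe the result as the effect of the film plus encouraged re-watching.
3. Report re-watch counts by arm.
4. If a direct effect is still of interest, run the re-watch-adjusted model as a labelled supplementary analysis. Give it an arm-by-re-watch term, read it at zero re-watches, and state the assumption of no unmeasured common causes of re-watching and T3 outcome. The interaction deals with the common slope but not with confounding, so H7 should not rest on this model.
5. Do not attribute a T3 effect to parent-child conversations. H7 expects its effect "relative to the control groups based on parent-child conversations on topics related to positive body image", but no measure described in the article captures them. The T3 parent survey is not itemised in full, so this is a limit on interpretation and not a claim that the item is absent.

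The cost is wording in two sections and in the analysis plan, with no new data. The downside is that RQ7 no longer claims to be net of re-watching, which covariate adjustment alone cannot deliver.
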